## Methods: participants, interventions, and outcomes

### Study setting {9}

The comparison between the FASTER and SCOTT&EVA interventions and TAU will be implemented as a national interventional multi-center trial at six centers in Germany. Six centers in Germany take part in the recruitment and implementation of the study. The list of recruiting study sites can be obtained from the German Clinical Trial Register with the register number DRKS00017817 (internet site: https://www.drks.de/drks_web/navigate.do?navigationId=trial. HTML&TRIAL_ID=DRKS00017817).

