## Assignment of interventions: allocation

### Sequence generation {16a}

Subjects are randomized by cluster randomization in an allocation ratio of 1:1:1. The cluster size is set to 6 patients per cluster. This means that groups of 6 participants are built within each center, and these groups are randomly assigned to one of the three study arms. The randomization will not be stratified by center or other factors. An Internet-based randomization system (http://www.randomizer.at) will be used and the allocation sequence is created by computer-generated random numbers.

All transactions will be logged. The software’s GCP-compliance has been confirmed by the Austrian Federal Office for Safety in Health Care (BASG). Details of the randomization scheme will be specified in an external document accessible to the Institute of Medical Biometry and Informatics (IMBI, Heidelberg) only to minimize selection bias.

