#### Analysis

Let μ denote the unknown true mean difference of the SRS-A score between baseline and 4 months after baseline. The following two primary local test problems are assessed:
$$ {\mathrm{H}}_{0,\mathrm{SCOTT}\&\mathrm{EVA}}:{\upmu}_{\mathrm{SCOTT}\&\mathrm{EVA}}={\upmu}_{\mathrm{TAU}}\ \mathrm{versus}\ {\mathrm{H}}_1:{\upmu}_{\mathrm{SCOTT}\&\mathrm{EVA}}\ne {\upmu}_{\mathrm{TAU}} $$

and
$$ {\mathrm{H}}_{0,\mathrm{FASTER}}:{\upmu}_{\mathrm{FASTER}}={\upmu}_{\mathrm{TAU}}\ \mathrm{versus}\ {\mathrm{H}}_1:{\upmu}_{\mathrm{FASTER}}\ne {\upmu}_{\mathrm{TAU}} $$

The aim is to show that at least one of the two local alternative hypotheses holds true. For each pairwise comparison (TAU versus FASTER and TAU versus SCOTT&EVA) a Mixed Model Repeated Measures (MMRM) will be applied. It includes the difference of the SRS-A score between baseline and 4 months after baseline as the dependent variable, the baseline SRS-A score, and the group allocation as fixed effects, and the center and the cluster as random effects. The MMRM uses all available changes from baseline SRS-A score for all patients for model estimation. In the “Sample size {14}” section, the local significance level of .026632 has been deduced. In case that at least one of the null hypotheses specified above can be rejected at the local significance levels of .026632, we hierarchically assess additionally the following test problem:
$$ {\mathrm{H}}_{0,\mathrm{SCOFA}}:{\upmu}_{\mathrm{SCOTT}\&\mathrm{EVA}}={\upmu}_{\mathrm{FASTER}}\ \mathrm{versus}\ {\mathrm{H}}_1:{\upmu}_{\mathrm{SCOTT}\&\mathrm{EVA}}\ne {\upmu}_{\mathrm{FASTER}} $$

at the full two-sided level of 0.05 in a confirmatory manner. In case neither H0, SCOTT&EVA nor H0, FASTER can be rejected, the comparison between the FASTER and the SCOTT&EVA arm is done descriptively. The confirmatory analysis of the primary efficacy endpoint corresponds to the primary estimand and will be conducted in the full analysis set.

As a sensitivity analysis to the primary efficacy analysis, corresponding MMRMs with additional covariates/factors given by IQ, age, gender, ASD symptom severity, MET test result, and center will be conducted. Furthermore, the separate items of the SRS-A score are analyzed individually to investigate which items differ between the treatment groups. Details of these analyses will be specified in the statistical analysis plan (SAP).

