Exploratory analyses will investigate moderation of treatment effects by conducting the primary MMRM considering the following additional variables: IQ, age, gender, center, years of therapy experience with autism, depressiveness (BDI), self-confidence (MSWS), social competence (SASKO), and life events (FEL). To optimize treatment selection for individual patients, these covariates will be used to estimate individualized treatment effects from parameter estimates to construct optimal individualized treatment rules and to clarify for whom a treatment works best [47].

Descriptive methods will be used for the analysis of the secondary outcomes, including the calculation of appropriate summary measures of the empirical distribution as mean, median, standard deviation, 1st and 3rd quantile for continuous outcomes, and absolute and relative frequencies for count data. Furthermore, 95% confidence intervals and descriptive two-sided *p*-values will be reported. Graphical methods will be applied to visualize the findings. The safety analysis includes calculation of frequencies and rates of adverse and serious adverse events. Additionally, as supplementary analysis the primary endpoint will be evaluated in the per-protocol population. Furthermore, statistical methods are used to assess the quality of data. All analyses will be done using Statistical Analysis Software (SAS) version 9.4 or higher.

Analyses will be defined in detail in the SAP which has to be authorized before data base closure by the two involved biometricians and the lead investigator.

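### Center, a site attribute, is an input to the exploratory rules meant to choose treatment for individual patients

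*Protocol article*

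**What the plan says.** In the protocol article, *Statistical methods for primary and secondary outcomes {20a}*, *Analysis*, the exploratory moderator analysis extends the primary MMRM by nine variables. The list begins "IQ, age, gender, center, years of therapy experience with autism" and ends with measures of depression (BDI), self-worth (MSWS), social competence (SASKO) and life events (FEL). Center is the fourth. The next sentence gives the purpose, "To optimize treatment selection for individual patients", and the use: "these covariates will be used to estimate individualized treatment effects from parameter estimates to construct optimal individualized treatment rules". No listed variable is excepted.

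The primary model in the same section already has "the center and the cluster as random effects". On the design, *Study setting {9}* states: "Six centers in Germany take part in the recruitment and implementation of the study". *Sequence generation {16a}* forms clusters of six within each center and states: "The randomization will not be stratified by center or other factors". The analysis is labelled exploratory, and details are deferred to the SAP.

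**The concern.** A rule for choosing a patient's treatment should rest on what is known about that patient before treatment. Center is something else. A center-by-treatment coefficient mixes the local therapists, the composition of a handful of FASTER groups, the local content of usual care, and chance. Two otherwise identical patients could be directed to different programs only because of where they were recruited. A patient treated outside the six centers has no center coefficient, yet the trial is meant to support treatment of adults with ASD in Germany generally.

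The design also gives little information on center-specific effects. There are few clusters per center and arm, and nothing guarantees that every center receives every arm.

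The objection applies to center only. Years of therapy experience appears to be a patient variable, since years of earlier ASD treatment are collected under *Demographic and baseline information*.

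**Working it through.** **Inputs from the article** (*Sample size {14}*, *Sequence generation {16a}*, *Study setting {9}*): 360 patients, clusters of 6, allocation 1:1:1, six centers, ICC 0.05 in FASTER and 0.01 in SCOTT&EVA and TAU, baseline correlation 0.2, effect 0.4 versus TAU, drop-out 25%.

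**Assumption:** center sizes are not given. Equal centers are the base case, with two unequal splits as a range.

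**1. The plan's own figure.** The ANCOVA variance factor is 1 − 0.2² = 0.96. The design effects are 1 + 5 × 0.05 = 1.25 and 1 + 5 × 0.01 = 1.05. The correlation of the two tests is 1/√(2.10 × 2.30) = 0.455. At local level 0.026632, the power to reject at least one hypothesis is 0.8015 with 87 per group and 0.7969 with 86. So 87 reproduces. Then 87/0.75 = 116, rounded up to a multiple of 6, gives 120 per group.

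**2. Information per center.** 360/6 = 60 clusters, 20 per arm. Equal centers have 10 clusters each, or about 3.3 per arm. That is 20 patients randomized and 15 evaluable per arm and center.

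**3. Precision of a center-specific FASTER minus SCOTT&EVA contrast.** With balanced arms, SE = √(0.96 × (1.25 + 1.05)/n). This is 0.33 for n = 20 and 0.38 for n = 15. Clusters do not split evenly within centers, so the realized SD is larger, as step 4 shows.

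**4. Simulation with no true difference between programs or centers.** 20,000 runs per scenario: 60 clusters permuted to 20/20/20, observed cluster size binomial(6, 0.75) with minimum 1, cluster-mean variance 0.96 × (ICC + (1 − ICC)/m). Shrunken results use a moment estimate of a random center-by-treatment variance.

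| Clusters per center | SD of contrast | Mean spread, unshrunken | Mean spread, shrunken | Opposite programs, unshrunken | Opposite programs, shrunken | Some center lacks FASTER or SCOTT&EVA |
|---|---|---|---|---|---|---|
| 10 in each | 0.42 | 1.06 | 0.19 | 96% | 27% | 13% |
| 16/12/10/9/7/6 | 0.44 | 1.08 | 0.19 | 95–96% | 27% | 28% |
| 20/14/10/8/5/3 | 0.45 | 1.04 | 0.18 | 93–94% | 26% | 69% |

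The spread is the difference between the highest and lowest center, in SD units. As a check, the expected range of six independent normal values is 2.534 SDs, and 2.534 × 0.42 = 1.06. With shrinkage, the estimated center-by-treatment variance is zero in about 59% of trials, so the median spread is 0.

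**5. Missing arms, by hand for equal centers.** The chance that a given center receives none of the 20 FASTER clusters is C(40,10)/C(60,10) = 0.0112. Six centers and two programs give an upper bound of 12 × 0.0112 = 0.135, in line with the simulated 13%. Counting TAU as well, some arm is missing in some center in about 18% of trials, or about 27% if each cluster is allocated independently rather than to fixed totals.

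**The case against.** The strongest reply is that the article does not say how center would enter. The moderator analysis extends a model in which center is random. A random center-by-treatment term would pull chance differences together: the spread falls from about 1.05 to about 0.2 SD, and opposite recommendations fall to about a quarter of null trials. This stands. The unshrunken figures are an upper case, not what the plan must produce.

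Several stronger readings are tempting and should not be drawn:

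- **That the rule could not be used at all outside the six centers.** Center could be averaged out or set to its mean. The article does not say this will be done, but nothing rules it out.
- **That the roughly 96% of trials with opposite recommendations shows how noisy centers are.** Six independent null contrasts disagree in sign with probability 1 − 2/64 = 96.9% at any precision, so this figure says nothing about the size of the noise.
- **That missing arms are likely.** The 28% and 69% come from assumed center sizes. The article gives none, and it places the details of the randomization scheme in a separate document.

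It is also fair that exploring treatment-by-center heterogeneity is normal in a multi-center trial of therapist-delivered treatment, and that coding and shrinkage belong to the SAP. Neither point answers the concern. Center is named in the article as an input to a patient-level rule, and that is a stated choice, not an omitted detail.

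**Conclusion.** The point holds as a modest one. Followed as written, the plan puts a site attribute into a rule meant for individual patients. The rule then gives no direct recommendation elsewhere unless center is averaged out. Within the six centers it draws on contrasts whose chance SD (0.42 to 0.45 unshrunken) is as large as the planned effect of 0.4 versus TAU. Shrinkage would reduce the problem considerably but would not make center a patient characteristic.

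The figures rest on the plan's ICCs, correlation and drop-out rate, on no true heterogeneity, and on assumed center sizes. The 13% for a missing program is for equal centers and fixed 20/20/20 totals.

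A reader might infer that the trial's main conclusions are at risk. They are not: the analysis is exploratory, and the confirmatory tests, the local level and the 87/120/360 sample size are untouched. Nor would removing center alone make the rule usable at the time of treatment choice. The life-event list (FEL) in the same set is scheduled only at T1 and T2 in Table 1, so it is not available at baseline.

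**What to change.** In the exploratory paragraph of *Analysis* ({20a}), and correspondingly in the SAP before it is authorized, remove center from the covariates that feed the individualized treatment effects and rules. Keep center as the random effect of the primary model. If variation of the treatment effect between centers is of interest, report it separately as heterogeneity, for example as a random center-by-treatment variance, and not as a basis for choosing a patient's treatment.

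This costs one line, with no extra data or patients and no change in power. The small downside is that center no longer enters the rule. The post-baseline timing of FEL needs its own correction.

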### Outcomes {12}

All outcomes will be assessed at baseline (T0), post-treatment (T1, 4 months after baseline), and follow-up (T2, 8 months after baseline).

The primary endpoint of our trial is the change of the total sum score from baseline (T0) to 4 months after baseline (T1) in social responsiveness as measured with the *Social Responsiveness Scale* (SRS-A adult, parent/spouse/other, [18, 19]).

The secondary outcome measures aim to differentially assess aspects of self-reported social responsiveness, social cognition, social skills, empathy, common comorbid psychopathology, self-esteem, life satisfaction, and quality of life. Almost all questionnaires and tests (see Table 1) are well-established, widely-used instruments with excellent psychometric properties (see also the “Data collection and management” section).

The measurement for social responsiveness (parent/spouse/other) at the follow-up measurement time point (T2) is also a secondary outcome.

**Table 1 Tab1:** Illustration of frequency of study visits, questionnaires, and tests

	SCR	T0	T1	T2
GAF (SCR: via telephone or personally)	x^1^	x^3^	x	x
Psychopharmacotherapy	x^1^	x	x	x
ADOS-2 (if lacking)	x^2^			
SCID-5-CV	x^2^			
CFT 20-R	x^2^			
MWT-B	x^2^			
Neo-FFI	x^2^			
AQ50	x^2^			
EQ40	x^2^			
WURS-K	x^2^			
ADHS-SB	x^2^			
TAS-26	x^2^			
Basis Documentation	x^2^			
SRS-A (patient)		x	x	x
SRS-A (parent/spouse/other)		x	x	x
SRS-A mod. (patient)			x	x
SRS-A mod. (parent/spouse/other)			x	x
MET (computer test)		x	x	x
BDI-II		x	x	x
SASKO		x	x	x
MSWS		x	x	x
FLZ^M^		x	x	x
WHOQoL-Bref		x	x	x
Freiburg Event List			x	x
Partnership Questionnaire (if appropriate)		x	x	x

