Two other questionnaires have been constructed in Freiburg especially for adults with autism and are not validated until now. We use specifically formulated questions for potentially occurring life events and a partnership questionnaire where either partners or only one may be autistic. To date, no comparable questionnaires are available in Germany.

The *Freiburg Event List* (FEL) will be used to assess non-treatment life events and is included to evaluate possible moderation effects at post-treatment and follow-up.

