### Adverse event reporting and harms {22}

Following ICH-GCP, the definition of an adverse event (AE) is adapted as follows: an AE is any untoward occurrence in a subject participating in a study, which does not necessarily have a causal relationship with the study treatment. An AE can therefore be any unfavorable and unintended sign, symptom, or disease temporally occurring alongside with the treatment (FASTER/SCOTT&EVA/TAU), whether or not related to the treatment.

The following will be defined as adverse events for the treatment study FASTER/SCOTT&EVA:
Increase of comorbid symptoms, e.g., substantial depression symptoms from none or mild to moderate symptoms ≥19 (BDI-II) or a significant worsening from moderate to severe symptoms (≥ 30); severe obsessive-compulsive or anxiety disorder; constant and excessive interactional problems (dispute with group members) or sensory overflow that prevent participation in group therapy.Significant recurrence of comorbid disorders.Appearance of new comorbid symptoms/disorders as described in 1 or new diagnosis.Occurrence of new passive suicidal thoughts (suicide questionnaire, item 4 and 5 positive).Occurrence of active suicidal thoughts or plans (suicide questionnaire, item 6 or higher positive).Changes in medication class (not dose adjustment) of antidepressants, benzodiazepines, typical or atypical neuroleptics, stimulants, and mood stabilizers.Occurrence of constant and excessive problems in the relationship between patient and therapist.Private burdens like divorce, death of a family member, and relocation.Occupational burdens like job change, loss of employment, or significant changes in frame conditions of existing employment.Vocational reintegration burdens (measures by the employment office; rehabilitation measures, which lead to conflicts of dates with the study intervention).

A pre-existing disorder or symptom will not be considered an adverse event unless there will be an untoward change in its intensity, frequency or quality. This change will be documented by an investigator.

Surgical procedures themselves are not AEs; they are therapeutic measures for conditions that require surgery. The condition for which the surgery is required may be an AE. Planned surgical measures permitted by the clinical trial protocol and the condition(s) leading to these measures are not AEs if the condition leading to the measure was present prior to inclusion into the trial.

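### Life events (FEL), collected only after randomization, are an input to rules for choosing treatment, so the rules cannot be computed when treatment is chosen

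*Protocol article*

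**What the plan says.** The Analysis subsection of the protocol article (under Statistical methods {20a}) plans exploratory moderation analyses that add nine variables to the primary MMRM: IQ, age, gender, center, years of therapy experience with autism, BDI, MSWS, SASKO and FEL. It then carries the list forward without exception: "social competence (SASKO), and life events (FEL). To optimize treatment selection for individual patients, these covariates will be used to estimate individualized treatment effects". The stated aim is "to construct optimal individualized treatment rules and to clarify for whom a treatment works best".

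Two places fix when the FEL is collected:

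- Table 1 in Outcomes {12} has the columns SCR, T0, T1 and T2. The row reads "Freiburg Event List x x", with both marks under T1 and T2 and nothing under SCR or T0.
- The Secondary outcomes subsection says that the FEL "will be used to assess non-treatment life events and is included to evaluate possible moderation effects at post-treatment and follow-up".

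Intervention description {11a}, Table 2 and Who will be blinded {17a} all place randomization after the T0 assessment.

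**The concern.** A rule for selecting treatment can use only what is known when the selection is made. If the fitted rule includes the FEL, a clinician facing a new patient has no value to enter, because the questionnaire is scheduled at the end of treatment and at follow-up. The analysis would then not deliver what the section promises, which is guidance on who should receive which program.

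A second, conditional worry concerns the moderation estimates themselves. Every FEL value is recorded after allocation. If FASTER or SCOTT&EVA changes which life events occur, or how strongly those events go with the outcome, then effects estimated given the FEL mix the effect of treatment with a consequence of treatment.

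**Working it through.** The main point needs no arithmetic, and the plan gives no figure for it. It follows from setting the places side by side.

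1. **Input to the rule.** The Analysis subsection names the FEL in the list and refers back to that list as a whole.
2. **Time of measurement.** Table 1: T1 (4 months) and T2 (8 months) only. The Secondary outcomes text agrees.
3. **Time of allocation.** After T0 and before treatment starts.
4. **Result.** Every FEL value is post-randomization. The T1 value is collected at the same visit as the primary outcome, and the T2 value comes after it. None exists at the point of choice.
5. **Remaining inputs.** Nine minus one leaves eight. BDI-II, MSWS and SASKO are marked at T0 in Table 1. IQ tests and basic documentation (age, gender, therapy history) belong to screening, and center is known at enrolment. I read years of therapy experience as the patient's therapy history recorded at screening.

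For the conditional point, a small linear illustration shows why no size can be given. Only the effect of 0.4 SD comes from the protocol (Sample size {14}), written here as -0.40; all other values are assumptions. Let the FEL have unit variance within each arm, let treatment shift it by *s*, and let an unmeasured cause load *a* on the FEL and *b* on the outcome. The within-arm slope of outcome on FEL is then *ab*, and

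arm effect at mean FEL = -0.40 - *ab* x *s*.

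| Assumption | Calculation | Arm effect | Arm-by-FEL interaction |
|---|---|---|---|
| *s* = 0, *a* = *b* = 0.5 | -0.40 - 0.25 x 0 | -0.40 | 0 |
| *s* = -0.2, *a* = *b* = 0.5 | -0.40 + 0.25 x 0.2 | -0.35 | 0 |
| *s* = -0.4, *a* = *b* = 0.5 | -0.40 + 0.25 x 0.4 | -0.30 | 0 |
| *s* = +0.15, *a* = 0.6, *b* = 0.5 | -0.40 - 0.30 x 0.15 | -0.445 | 0 |
| *s* = +0.30, *a* = 0.6, *b* = 0.5 | -0.40 - 0.30 x 0.30 | -0.49 | 0 |
| *s* = 0, *a* = 0.6 in control and 0.2 in treated, *b* = 0.5 | slopes 0.30 and 0.10 | -0.40 | 0.10 - 0.30 = -0.20 |

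Simulations with 240 patients in two arms agree for the first three rows and the last: -0.398, -0.348 and -0.299 for the arm effect, and -0.197 for the last interaction. The shift can move the arm effect either way or not at all. A false interaction, which is what a moderation analysis targets, appears only when treatment changes the link between the unmeasured cause and the FEL.

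**The case against.** The best defence is that the protocol describes the FEL as recording events outside treatment. An external event during the treatment period can genuinely modify an effect, so a reader who infers that a variable measured after randomization can never be studied as a moderator goes too far. If treatment leaves life events and their link to outcome alone, the first row of the table applies and there is no bias. This stands, and it rules out saying that the estimates will be biased or attaching a percentage to the bias.

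The label is nevertheless an assumption. Background and rationale {6a} ties unemployment to communication difficulties at work, which the programs aim to improve. The Secondary outcomes subsection says that the FEL is not yet validated, and participants know their allocation.

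Three stronger readings are tempting but not supported:

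- **That the FEL records the same events as the adverse event list**, for example "Private burdens like divorce, death of a family member, and relocation". The FEL items and recall period are not given, so the overlap is a guess. Adverse events are also defined without requiring a causal link to treatment.
- **That BDI-II, MSWS, SASKO or MET would be entered at the wrong visit, or without interaction terms.** All four are collected at T0, nothing says that later values will be used, and a stated aim of investigating moderation implies interactions. Such detail belongs in the SAP.
- **That the FEL must be removed from all moderation work.** That would discard its stated purpose, and the problem with the rule does not require it.

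One sentence in Outcomes {12} might seem to supply a baseline value: "All outcomes will be assessed at baseline (T0), post-treatment (T1, 4 months after baseline), and follow-up (T2, 8 months after baseline". Table 1 and the FEL description are specific and say otherwise, so it does not.

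None of this answers the point about the rule. For the other questionnaires the SAP can specify T0 values; for the FEL there is none to specify.

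**Conclusion.** The point holds for the treatment rules. As written, they take an input that is unavailable at the time of choice for every future patient, whether or not the programs affect life events. This rests on the Table 1 schedule and on reading the reference to the covariates as covering the full list, which is what the text says.

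The point about bias holds only conditionally. FEL moderation estimates could be biased if the programs influence life events or their relation to outcome, and the documents settle neither size nor direction.

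A reader might infer that the trial's main conclusions are at risk. They are not. The primary MMRM, the local level of 0.026632, the 87 patients per group and the total of 360 do not involve the FEL. One of nine variables in an analysis declared exploratory is affected, so this is a minor correction.

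**What to change.** In the exploratory paragraph of the Analysis subsection, state that inputs to the individualized treatment rules are restricted to variables measured at or before T0. This excludes the FEL and leaves the eight other listed variables.

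Report the FEL by arm. If FEL moderation is still of interest, present it as a separate analysis, say that it conditions on a post-randomization variable, and state the assumption that treatment does not affect the FEL. Reconcile the general sentence in Outcomes {12} about assessing all outcomes at T0 with the FEL row of Table 1.

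The cost is a change of wording and one exploratory variable lost from the rule. Confirmatory tests, significance levels and sample size stay as they are.
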